### Sample size

As the main objective is to establish feasibility parameters for a definitive trial, there are no formal sample size calculations, interim analyses or stopping rules.

### Qualitative research

Qualitative interviews will be used with approximately 12 participants to inform the future development and use of the intervention. The interviews will consider whether the VUSE and VRV treatment was acceptable, engaging and relevant. A particular focus will be on the acceptability and experience of the virtual reality. Participants will be invited to be involved in the interviews after the end of treatment at the 12-week assessment point, and interviews will ideally be conducted before the 16-week scheduled assessment but can be undertaken up to 20 weeks from enrolment in the study if there are issues in arranging visits etc. Topic guides for semi-structured interviews will be co-developed with the Patient Public Involvement (PPI) group and piloted in advance. Participant numbers should provide sufficient data to meet criteria for trustworthiness of the findings.

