**Methods and analysis:**

The study is a single arm feasibility trial (n=16) evaluating VUSE+VRV and treatment as usual. The study is recruiting people with psychosis and distressing VHs in one NHS Trust and uses independent but non-blind research assistants to undertake assessments before, during and after treatment (at baseline, 6, 12 week) and at follow-up (16 weeks). Quantitative information on recruitment rates, adherence and completion of outcome assessments (VHs, other psychiatric symptoms, quality of life and perceived recovery) will be collected. Qualitative interviews will capture service-users’ experience of therapy. Analyses will focus on feasibility outcomes and provide initial estimates of intervention effects. Thematic analysis of the qualitative interviews will assess the acceptability of the intervention.

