### Assessments

Basic demographic and clinical data will be collected (eg, age, gender, ethnicity, clinical diagnosis) at baseline. Clinical outcomes including VH, psychosis and affective symptoms, functioning and quality of life will be assessed at all four time points (baseline, mid treatment (post VUSE sessions at 6 weeks), post VRV intervention (12 weeks) and follow-up (16 weeks).

In terms of primary outcomes, the presence of distressing VH (and their frequency, duration, content) will be confirmed using the North East Visual Hallucination Inventory (NEVHI^37^). The distress and impact of the VH will be measured using the Psychotic Symptoms Rating Scale^38^ adapted for use with visions^26^ and a self-report measure the Hamilton Programme for Schizophrenia Voices Questionnaire^39^ which has been adapted for use with people with VH.^14 27^ In terms of secondary outcomes, hallucinations in other modalities will be collected for lifetime occurrence using the Multi-Modality Unusual Sensory Experiences Questionnaire^40^ and for the past month using the Multimodal Hallucinations Measure.^17 21^

Other secondary outcomes include quality of life assessed using the Questionnaire about the Process of Recovery,^41^ functioning (DIALOG^42^), paranoia (Green Paranoid Thoughts Scale revised^43^), levels of depression (Patient Health Questionnaire-9 PHQ9^44^) and anxiety (Generalised Anxiety Disorder Scale^45^) and stigma (Internalised Stigma of Mental Illness Scale^46^). Service use data will be collected with an adapted version of the Client Service Receipt Interview^47^ and experience of therapy assessed using the working alliance inventory^48^ and satisfaction with therapy (Satisfaction with Therapy and Therapist Scale-Revised^49^) will be undertaken at the end of the treatment period. Data will be reported in line with the Consolidated Standards of Reporting Trials (CONSORT)—Social and Psychological Interventions (CONSORT-SPI) statement^50^ and Standard Protocol Items: Recommendations for Interventional Trials (SPIRIT) guidelines.^51^ This guidance recommends minimising the distinction between primary and secondary outcomes so all outcomes will be reported at the end of the trial.

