### Criteria for proceeding to a full trial

We will use criteria for assessing study success and identifying feasibility factors required for delivering the definitive study and follow a systematic process for decision making after pilot and feasibility trials which helps identify criteria used to go to a full trial.^55^ These criteria are being developed with the PPI group to help determine if a full trial is warranted but will likely include participant recruitment, adherence with the intervention, retention of participants, intervention fidelity and acceptability to assess the trial. This will use both quantitative and qualitative data derived from the study. The progression criteria will be divided into three categories (green, red and amber). Areas that are amenable to change before a feasibility trial will be investigated and solutions discussed with the PPI group for acceptability. This will help consider if a further trial is timely, necessary and deliverable.

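### Direct evidence on acceptability is first sought at the end of treatment (week 12), so anyone lost before then contributes none and the picture will tend to be too favourable

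*Protocol article*

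**What the plan says.** Two sources in the protocol article ask participants directly how they found the therapy, and both are placed at or after the end of treatment.

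- **Interviews** (Qualitative research). "Qualitative interviews will be used with approximately 12 participants", and the approach is timed as follows: "Participants will be invited to be involved in the interviews after the end of treatment at the 12-week assessment point". The aim is to interview before the 16-week visit, but an interview "can be undertaken up to 20 weeks from enrolment in the study if there are issues in arranging visits etc".
- **Scales** (Assessments). The article has "experience of therapy assessed using the working alliance inventory" and a satisfaction scale, and states that this "will be undertaken at the end of the treatment period".

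The session-by-session ratings described under Analysis cover the frequency, distress and impact of the hallucinations. They do not rate the therapy.

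Acceptability carries weight in this study. It is named under Research question. The Abstract says that the thematic analysis of the interviews is what will assess it. The section Criteria for proceeding to a full trial lists, among the likely criteria, "adherence with the intervention, retention of participants, intervention fidelity and acceptability".

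**The concern.** The treatment deliberately puts people in front of a representation of a vision that frightens them. A person who gives up after a first VR session, and perhaps drops out of the study as well, knows something that nobody else in the sample can report. That person is also among the least likely to be present at week 12.

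If the direct evidence comes only from people still in contact then, the study can reach a favourable view of acceptability without having heard why anyone left. Two things are at stake: the progression judgement, and the information needed to revise the treatment before a further trial. The reasons for leaving are hard to recover once contact is lost.

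**Working it through.** The article gives no sample-size calculation and no expected dropout, so there is no planned figure to reproduce. The check is a comparison of timings followed by a count.

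**1. Who can be reached under the stated timing**

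| Participant | Reached by the week-12 invitation? | Direct evidence on acceptability |
|---|---|---|
| Completes VUSE and VRV | Yes | Interview and scales |
| Stops therapy, stays in the study | Yes, at the scheduled visit | Possible, but recalled later |
| Lost to the study before week 12 | No | None from the procedures described |

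On the delay in the second row: someone who stops at about the 6-week assessment would be approached 12 − 6 = 6 weeks later, and could be interviewed as late as 20 − 6 = 14 weeks later.

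**2. Whether the interview number protects against this**

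Inputs: N = 16 enrolled (Abstract, Trial design) and about I = 12 interviews (Qualitative research). The number lost before week 12, d, is not given and is varied here.

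- People still in the study: 16 − d.
- Interviews they can fill on their own: min(12, 16 − d).
- Leavers expected among 12 interviewees if they were included in proportion: d × 12/16.

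| d | d/16 | Still in study | Interviews they can fill | Leavers among 12 if proportionate |
|---|---|---|---|---|
| 0 | 0% | 16 | 12 | 0 |
| 2 | 12.5% | 14 | 12 | 1.5 |
| 4 | 25% | 12 | 12 | 3 |
| 5 | 31% | 11 | 11 | 3.75 |
| 6 | 37.5% | 10 | 10 | 4.5 |

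Up to d = 4, the planned number is met without hearing from any leaver. Only from d = 5 would a shortfall show that someone is missing.

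Chance alone would rarely produce this. If 12 of the 16 were drawn at random, the probability of drawing no leaver would be C(14,12)/C(16,12) = 91/1820 = 5% with two leavers, and C(12,12)/C(16,12) = 1/1820 = 0.05% with four. An all-stayer set of interviews would therefore be mainly a product of when people are asked.

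**3. Direction**

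Let s be the share of stayers who find the treatment acceptable and l the share of leavers. A view from stayers alone exceeds the view from all 16 by

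s − [(16 − d)s + d·l]/16 = d(s − l)/16.

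This is positive whenever l is below s. That leavers find the treatment less acceptable is an assumption, though a natural one. The document gives neither s, l nor d, so the formula supplies a sign and not a size.

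**The case against.** The strongest reply is that the 12-week assessment is not a filter for completers. It is a scheduled visit for all participants, nothing in the article makes it depend on finishing therapy, and the invitation is addressed to participants in general. This stands. A reader might infer that only finishers can be interviewed, or that anyone who stops VR is excluded. The text does not support that: someone who stops therapy but remains in the study can be invited at week 12 and interviewed up to week 20. The gap is confined to people lost earlier, plus delayed recall for those who stopped earlier and stayed.

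Second, other information bears on acceptability. Adherence and retention are counted for the whole sample and sit beside acceptability among the likely progression criteria. Formal complaints about therapy are a prespecified event, and the therapist telephones between sessions. So a progression decision would not rest on finishers' views alone. This also stands, but these sources record that someone left or complained. They are not a systematic account of why.

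Third, the Trial design section refers to a full protocol for detail when it introduces the interviews. How interviewees are sampled and how people who stop are approached may be set out there. The point is therefore limited to the timing that the article itself states, and it falls away if the full protocol already provides for contact at the time of stopping.

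Finally, it is tempting to put a percentage on the bias. With 90% of stayers and 20% to 50% of leavers assumed to find the treatment acceptable, and 2 to 6 leavers, the formula gives 2 × 0.40/16 = 5 points up to 6 × 0.70/16 = 26 points. All of these inputs are assumed, and the planned inductive thematic analysis yields no percentage acceptable, so this is not a forecast of what the study would report. Nor does the figure of about 12 apply to the scales; it is stated for the interviews only.

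**Conclusion.** The point holds in a limited form. Followed as written, the article's timing yields no direct evidence on acceptability from anyone lost before week 12, and with up to 4 leavers out of 16 the interviews can be completed without them. If leavers find the treatment less acceptable than stayers, the acceptability evidence used for progression will be too favourable. The size of that effect cannot be derived from the document. If nobody is lost before week 12, this gap does not arise. The change is worth making because it is cheap and the direction of the error is predictable.

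**What to change.** Add to the interview and assessment procedures:

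- For anyone who stops VUSE or VRV early, or withdraws, offer the same interview and the same alliance and satisfaction scales at the time of stopping. Keep the 12-week invitation for everyone else.
- Give non-completers priority within the roughly 12 interviews.
- For each acceptability source (interviews, alliance, satisfaction), report how many completers and how many non-completers contributed, out of the 16 enrolled.
- Show non-completers' scale scores separately, because they reflect a shorter exposure to treatment.

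The number of interviews and the instruments stay the same. Some leavers will decline, and the reported counts will make that visible. A minor amendment may be needed. If the full protocol already provides for this, a sentence in the article saying so is enough.

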### Qualitative analysis

Qualitative data, gathered from the structured interviews with participants, will be analysed using an inductive thematic analysis.^54^ This form of analysis allows for both basic and more complex themes to be classified from interview data (based on categorising sections of transcripts), based on the data themselves rather than a prior theory. Transcripts will be coded by the research assistant and qualitative lead. Quotes to illustrate each category will be selected. Understanding of the data will be developed with PPI members.

### Criteria for proceeding to a full trial

We will use criteria for assessing study success and identifying feasibility factors required for delivering the definitive study and follow a systematic process for decision making after pilot and feasibility trials which helps identify criteria used to go to a full trial.^55^ These criteria are being developed with the PPI group to help determine if a full trial is warranted but will likely include participant recruitment, adherence with the intervention, retention of participants, intervention fidelity and acceptability to assess the trial. This will use both quantitative and qualitative data derived from the study. The progression criteria will be divided into three categories (green, red and amber). Areas that are amenable to change before a feasibility trial will be investigated and solutions discussed with the PPI group for acceptability. This will help consider if a further trial is timely, necessary and deliverable.

### The VUSE and VRV intervention

The treatment will be delivered by a qualified, trained and supervised psychological therapist. The person with VH will be seen face-to-face. The treatment consists of three stages described below.

#### Description of the VH

The initial session elicits a detailed description of the VH which will be shared with the VR programmers to allow a person-specific representation of their VH to be developed. The person identifies a visual experience they want to work on in the VR, one that causes distress and impact and is seen frequently enough to be helpful to work on. People with visions typically report seeing faces, people, figures, animals and objects (^19 20^which are also captured on the NEVHI^37^). The assessment is used to create a story board that first describes the setting in which the vision is seen (a living room, bedroom or garden, for example). Key information about the layout, background noises, lighting, time of day etc, is captured. Next, information about the vision (size, shape, colour, movement, sounds, facial features etc) is asked about and the person is encouraged to help represent this by drawing or describing the image, or using images from the internet. Finally, any additional information that makes the vision more impactful is captured, such as it moving towards the person or looking at them in a particular way (see online supplemental materials 2).

#### VUSE

During the programming time (~3 weeks) the therapist and service user work through the VUSE package over 4–6 weekly sessions (~60 min per session), to understand the causes of VH and foster new skills for their management. The treatment draws on the most helpful and valued modules from the MUSE package and has been developed further by PPI input to cover:

#### What are visions?

This provides normalising information about the frequency of VH (or the term used in the package is visions) and the factors that tend to increase visions (for example, isolation and sleep deprivation), along with testimonies from other people with visions providing powerful messages that the person is not alone, and that recovery from or living well with visions is possible.

#### How the mind works

This module explains what can lead to people seeing things others do not. It explains how our visual perceptual system can lead to mistaken perceptions, and it can lead to predictable and expected errors or illusions.^56^ For example, how we easily see faces in everyday objects as a result of our brains being equipped with a neural circuitry specialised for preferentially processing faces.^57^ This places visions in the context of being normal in that they result from a perceptual system that can be put under strain by processes like poor sleep or higher stress, which can increase the risk of making these sorts of mistakes. Key psychological processes such as heightened visual imagery, trauma, expectancy and threat detection are explained with engaging videos and animations. For example, the person may be provided with information about how memories from traumatic events are more likely to be experienced as intrusive memories without contextual cues and can therefore be experienced as belonging to the here and now. Based on these understandings, targeted coping strategies are introduced.

#### Assessment and formulation: identifying triggers, unhelpful appraisals and coping

This module starts by considering whether there are patterns or identifiable triggers/contexts associated with seeing visions. Commonly, they are experienced when tired or stressed, often when the person is alone or in the dark. Identifying these triggers can lead to simple changes (like substituting different activities or turning on lights at the time the vision is experienced) that can reduce the frequency or impact of visions. Next, key appraisals related to seeing the vision are elicited. These may be thoughts of harm to self or others as the vision represents a real threat. If the person perceives the vision as not real, then they may have fears of losing one’s mind. Other appraisals are that the visions will persist, or it may be that the content of what people see is distressing. These appraisals and resulting behaviours (leaving the room where they see a vision, trying to look away from the vision) are then linked to more helpful and constructive behaviours that are identified and practised in preparation for the VR session.

#### VRV

Following the VUSE sessions, the person attends the VR suite, which is a comfortable environment with a large screen on which the VR VH is displayed. The preference is to use the VR suite, but the option of using a VR headset (at their home or team clinical base) is possible and will be discussed with the participant. The person will have 4–6 sessions with the therapist present. There are four potential treatment approaches feasible within the VR environment. The first is exposure to the representation of the vision. This may help the person habituate to the presence of the VH and overcome the common tendency to leave when in the presence of the VH. Second, the participant will be encouraged to try behavioural experiments where they are supported in testing if the vision is real, perhaps by paying more attention to it and noticing characteristics that challenge if it is a real phenomenon (such as it having unusual features, or clothing). They will be further encouraged to test if it is real by practising throwing an object at it, or trying to photograph it on their phone. Third, people will be encouraged to explore safety beliefs, so that they practise dropping safety behaviours and defences, perhaps by turning their back on the vision to help show they are safer than they realise. Fourth, using the power of the VR environment, we can help the person develop control over their experiences by practising imagery transformation techniques that are commonly used in working with post-traumatic stress disorder or social anxiety to help change the power and intensity of the visual experience (such as changing its size or colour). The sessions will be recorded using video recording equipment in the VR suite (this will not be done if the person is using the headset option or is away from the VR suite). The therapist and participant will review these together after the session to enable the person to consider what they have learnt or done differently in the VR session, and a copy of the video is available to the person to take home and review to help them better manage when they see the vision away from the VR suite.

The therapist will call the participant in between scheduled sessions to check on progress with homework and to check on well-being.

### VR equipment

The XR/CBT Immersive Studio is a Class I Software as a Medical Device specifically developed to support healthcare professionals in conducting CBT and/or other talking therapies to support treatment of anxiety, phobias, depression and other mental health disorders. Through immersive scenes replicating anxiety-inducing scenarios, it creates controlled environments for patients to address their anxieties. The primary aim is to expedite patient recovery, particularly where graded exposure is a part of treatment.

### Details of the VR software

The VRV software application is composed of a set of virtual environments, including different scenes created using 3D models, ambient audio and 3D computer characters, with animations and speech. The environments are driven by source code which handles the logic of the programme, the behaviour of the computer characters, as well as the user interaction and data storage. The code is implemented on top of XRT background libraries and third-party libraries. The software is built using Unity (Unity Technologies). Unity acts as a render engine, displaying the virtual environments to the user through the VR suite or the headset.

### Treatment as usual

Participants will continue to receive their usual care which will typically consist of long-term prescription of psychiatric medications and meetings with a mental health practitioner. No restrictions will be placed on TAU though involvement in other psychological therapy will be discussed with the person and the team in case it leads to challenges in attending frequent appointments. We will collect detailed data on treatment as usual.

### Oversight

As the trial is unblinded and not randomised, a single trial oversight committee will combine the functions of a Trial Steering Committee and Data Monitoring Committee. The committee consists of an independent Chair, clinician, statistician and person with lived experience. There is a separate PPI group facilitated by two co-applicants for the study with lived experience of psychosis. The trial will be audited by the Sponsor at first participant and annually.

### Safety

In order to monitor for adverse events (AEs), we maintain close links with the participant’s clinical team throughout, have a staff member present throughout while the VR equipment is in use, and record events that we become aware of during a participant’s participation. We will also check the participant medical notes prior to each study visit for the following events pre-specified as adverse: (1) All deaths, (2) Suicide attempts, (3) Serious violent incidents, (4) Admissions to psychiatric hospital/secure units and (5) Formal complaints about therapy.

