#### Definitions of serious adverse events

A serious AE is defined by the ISO14155:2011 guidelines for medical device trials as an untoward medical occurrence that: results in death; is a life-threatening illness or injury; requires (voluntary or involuntary) hospitalisation or prolongation of existing hospitalisation; results in persistent or significant disability or incapacity; medical or surgical intervention required to prevent any of the above; leads to fetal distress, fetal death or consists of a congenital anomaly or birth defect or is otherwise considered medically significant by the investigator.

Life-threatening in the definition of a serious AE (SAE) refers to an event in which the subject was at risk of death at the time of the event. A planned hospitalisation for a pre-existing condition, without a serious deterioration in health, is not considered to be a serious AE. Admissions to psychiatric hospitals are not unexpected in this client group.

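### The scheduled notes search names only psychiatric admissions, but the serious-event definition covers hospitalisation of any kind, so unplanned general-hospital admissions depend on passive reporting

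*Protocol article*

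**What the plan says.** All references are to the protocol article.

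- **Safety, scheduled search.** "We will also check the participant medical notes prior to each study visit for the following events pre-specified as adverse". The list is numbered and closed at five: "1) All deaths, (2) Suicide attempts, (3) Serious violent incidents", then "4) Admissions to psychiatric hospital/secure units", and finally formal complaints about the therapy.
- **Safety, other routes.** The preceding sentence says "we maintain close links with the participant" and goes on to name that person's clinical team. It also places a staff member in the room during VR use and commits the team to "record events that we become aware of". The clinical-team link and the recording rule are not restricted by type of event.
- **Definitions of serious adverse events.** One criterion is that the occurrence "requires (voluntary or involuntary) hospitalisation or prolongation of existing hospitalisation". The stated exception is: "A planned hospitalisation for a pre-existing condition, without a serious deterioration in health, is not considered to be a serious AE". The section adds that psychiatric admissions are not unexpected in this population.
- **Definitions of adverse events.** Events count whether or not they are related to the intervention, from baseline to the end of the 16-week follow-up.
- **Assessments.** "Service use data will be collected with an adapted version of the Client Service Receipt Interview".

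**The concern.** The definition and the search are both printed in full, and they do not have the same scope. The definition does not depend on the type of hospital; the search's admission item does. A participant admitted unplanned to a general hospital for a medical or surgical reason has had a serious adverse event under the protocol's own rule, yet the person checking the notes has not been told to look for it.

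Two things are at stake. The first is the serious-event count, which the oversight committee will see and a later trial would draw on. Unrelated events belong in that count, so it cannot be argued that such admissions do not matter because they are probably unrelated. The second is timing. The Causality section attaches reporting timescales to related and unexpected serious events, and an event that is learned of late is assessed late.

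**Working it through.** The plan states no safety figure to reproduce, so the check is a comparison of texts.

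**Step 1: what is serious.** Under the definition, an untoward occurrence leading to admission, or to a longer stay, is serious. Type of hospital plays no part. The exception removes planned admissions for an existing condition that has not seriously worsened. What remains includes unplanned admissions to psychiatric and to general hospitals.

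**Step 2: what the scheduled search targets.**

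| Kind of unplanned admission | Serious by definition? | Target of the notes search? |
|---|---|---|
| Psychiatric hospital or secure unit | Yes | Yes, item (4) |
| General hospital, after a suicide attempt or serious violent incident, or ending in death | Yes | Yes, through items (1) to (3) |
| General hospital, any other cause | Yes | No |

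The gap is the third row. Other criteria in the definition, such as life-threatening illness or lasting disability, are likewise outside the five items unless they coincide with one of them.

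**Step 3: what catches the third row.** Two unrestricted routes remain: the link with the clinical team, and the recording of events that come to the team's notice. Neither is described as a scheduled, participant-by-participant question about hospital admission. The Participants section places the clinical teams in community mental health and early-intervention services. Whether such a team hears promptly of a general-hospital admission is not stated. The staff member present during VR covers only events in the session.

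**Step 4: how often this could matter.** The documents give no rate of general-hospital admission, so the following is an assumed range. If each of the 16 participants independently had probability p of an unplanned non-psychiatric admission in the reporting window, the chance of at least one in the trial is 1 − (1 − p)^16:

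- p = 1%: 1 − 0.99^16 ≈ 15%
- p = 5%: 1 − 0.95^16 ≈ 56%
- p = 10%: 1 − 0.90^16 ≈ 81%

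This is the chance that such an event **occurs**. It is not the chance that one is missed, which the documents do not allow anyone to estimate.

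**The case against.** The strongest reply is that the notes check is an additional measure, as its wording shows. General-hospital admissions already fall under the broad adverse-event definition and the two unrestricted routes. Contact is also frequent. Participants have 4–6 VUSE and 4–6 VRV sessions, so 8 to 12 in all, with well-being calls between scheduled sessions and assessments at baseline and at 6, 12 and 16 weeks. An admission during treatment would probably be noticed. This stands, and it rules out one reading that a reader might reach: that the count is bound to be incomplete. It may be incomplete, and no more can be said. The reply is weaker after treatment ends, when the article describes only the follow-up assessment and interviews with about 12 participants.

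A reader might also infer that the service-use interview is kept apart from safety reporting. The documents do not show that. An admission disclosed to the research assistant is something the team has become aware of, and such events are to be recorded. That no reconciliation step is described is silence in a condensed article, and the full protocol, which it cites, is not shown.

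A reader might finally size the problem by noting that one event in 16 is 6.25 percentage points (1/16). That is true of any event in any study of 16 people and does not measure how likely an admission is to be missed.

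One practical caveat also stands: the article does not say whether the notes available to the team contain general-hospital records. If they do not, a wider notes search would gain little by itself.

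**Conclusion.** The point holds in limited form. The pre-specified search is narrower than the protocol's own definition of a serious event. Unplanned general-hospital admissions that do not coincide with another listed event therefore rely on passive routes, and the serious-event count may be incomplete. Both texts appear in the article, so the mismatch does not depend on anything left to the full protocol.

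It is a moderate gap in ascertainment. The definition is not contradictory and no stated figure is in error. Its size in missed events is unknown, because it depends on the admission rate and on how reliably the passive routes work, and the documents give neither. The gap is worth closing because closing it is cheap and because this is a small, uncontrolled early test of a device-based treatment.

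**What to change.** 1. In Safety, align item (4) with the definition of serious adverse events, so that the notes check before each visit covers any unplanned hospital admission, psychiatric or general. The psychiatric and secure-unit admissions already listed should stay in.
2. As a low-cost cross-check, compare hospital admissions reported in the service-use interview with the adverse-event log. Enter any unmatched admission and assess it as the Causality section describes. This also helps if the notes do not show general-hospital care. If the full protocol already contains this step, a cross-reference is enough.

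Emergency-department attendance need not be added for this purpose, because attendance alone is not a criterion in the definition.

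The cost is one line in the list and a short comparison for 16 people, using notes already reviewed and data already collected. The downside is a few more unrelated events to log and assess. The interview cross-check improves completeness more than speed; the wider notes check before each visit is what helps with reporting timescales.
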